## Abstract

**Background:**

Obesity is currently a worldwide health crisis. Nurses are integral members of the primary health care team and have an important role in managing obesity and administering physical activity (PA) for patients. However, research shows that nurses tend to be overweight or obese, have poor metabolic health, and do not meet PA recommendations. This is problematic because PA is linked to both physiological and psychological well-being and may also influence how nurses counsel their patients. Nursing students are the next generation of nurses; however, there is limited research examining PA (among other lifestyle factors) and metabolic health in nursing students.

**Objective:**

The goal of this research is to examine multiple lifestyle factors (including PA, nutrition, sleep, and stress) and determine whether these factors are associated with metabolic health in full-time undergraduate nursing students.

**Methods:**

An estimated 320 nursing students (18 years of age and older) will be assessed for their metabolic health. Metabolic status will be determined by measuring body mass index (BMI), waist-to-hip ratio (WHR), body fat percentage [skinfold measures (FitSystems Inc)], resting blood pressure [automated oscillatory (Omron Healthcare Inc)], and fasting blood glucose (glucometer). Lifestyle factors will also be measured, including PA and sleep [the International Physical Activity Questionnaire (IPAQ) and 7-day accelerometry (wGT3X-BT, Actigraph LLC)], nutrition [3-day diet log (Nutritionist Pro, Axxya Systems)], and stress [the Depression Anxiety Stress Scale, heart rate variability assessments, and salivary cortisol (ELISA, Eagle Biosciences)]. The association between metabolic status and PA, sleep quantity and quality, nutrition, and stress will be examined by linear regression analyses. Differences by year of study in metabolic health status, PA, sleep, nutrition, and stress will be examined by 1-way analyses of variance (ANOVAs). To determine the ability of PA, sleep, nutrition, and stress to discriminate prevalent overweight and obesity or poor metabolic status, logistic regression and receiver operating characteristic (ROC) curves will be constructed. Statistical analyses will be performed in Stata (version 16.1, StataCorp LLC).

**Results:**

Based on pilot data, we believe senior nursing students will have worse metabolic health (ie, higher BMI and WHR, increased body fat percentage, higher blood pressure, and increased fasting blood glucose) compared to first-year students. We hypothesize that poor PA participation, poor sleep quantity and quality, increased food intake, poor nutrition, and increased stress will be associated with worse metabolic health in full-time nursing students. The study received funding in February 2020. Due to the coronavirus disease 2019 (COVID-19) pandemic, work on this study has been delayed. We are currently completing our application for institutional research ethics approval. Data collection is projected to begin in January 2021, with data collection and analyses expected to be completed by May 2022.

**Conclusions:**

This study will be the first published research to examine the relationship between lifestyle choices and metabolic status in nursing students attending a Canadian institution. More importantly, the results of this study will support the development of an informed intervention that will target the identified lifestyle factors, improving the physiological and mental health and well-being of nursing students.

**International Registered Report Identifier (IRRID):**

PRR1-10.2196/21342

## Introduction

### Background and Rationale

Obesity is a current international epidemic [1], and it has become a global priority to reduce the burden of obesity [2]. Primary health care workers, which include registered nurses (RNs), interact closely with patients and therefore have an important role in managing an individual's obesity and associated secondary diseases. The critical role of nurses as agents of change in addressing the issue of obesity has been highlighted [3]. Unfortunately, research suggests that RNs themselves have a high level of obesity [4,5], more than the general population [6]. In addition to high rates of obesity, RNs do not meet international recommendations of 150 minutes per week [7] of moderate to vigorous physical activity (PA) [8,9]. One study reported that less than 30% of RNs sampled engaged in moderate-intensity PA [10]. Another study found that average body mass index (BMI) placed RNs (n=400) in the overweight category (>27 kg/m^2^), and many had elevated waist circumference [11]. Furthermore, only 23% met the recommended PA guidelines [11]. Overall, research demonstrates that RNs tend to be overweight or obese and are not meeting exercise recommendations.

High obesity rates and sedentary behavior in RNs are particularly concerning for two reasons. First, a nurse's own behavior may influence their nursing practice. Indeed, RNs who exercise regularly are more likely to promote PA to their patients compared to those who are sedentary [10]. In addition to potentially impacting patient care, obesity and sedentary behavior in RNs are concerning because nurses are not optimizing their own physical and mental health. RNs who are overweight or obese suffer from impaired cardiovascular and metabolic health [11]. As well, the nursing profession is associated with high levels of psychological stress [12,13] and high rates of depression compared to the general population [14,15]. It is widely recognized that PA is important for maintaining both physiological and mental health [16,17]. Physical inactivity may actually worsen mental health in RNs; in one study, physical inactivity was associated with psychological distress, even after adjusting for age, job demands, and job control, among other factors [18]. Sleep also contributes to mental health and overall well-being [19], and RNs report being fatigued and having poor sleep habits [20-22]. Shift work is associated with higher BMI and waist-to-hip ratio (WHR) [23], while participation in PA is associated with improved sleep in non-nurse populations [24-27]. Thus, obesity, poor PA, and reduced sleep are concerning in RNs, considering the negative effect of such lifestyle choices on nurses' physiological and mental health.

Nursing students are a unique population of primary care providers as they are still engaged in education, and therefore, there is an opportunity to educate students regarding the importance of lifestyle choices for themselves and their patients. Unfortunately, research to date indicates that similar to RNs, nursing students also have poor physical fitness behaviors [28], and they tend to participate in less PA compared to non-nursing students [29]. However, there is limited published data that objectively characterizes obesity and PA in nursing students. Therefore, we recently conducted a pilot study that examined PA and overweight and obesity status in a small cohort of nursing students attending a Canadian institution [30]. BMI and WHR were measured, and PA was objectively assessed via 7-day accelerometry in 43 full-time nursing students. Participants were classified into 3 groups based on their nursing program year: first year (n=13), second year (n=10), and third/fourth year (n=20). Mean body weight was higher in second and third/fourth-year students compared to first-year students. Similarly, BMI was higher in second-year students (23.7 ± 1.9 kg/m^2^) and third/fourth-year students (25.4 ± 2.5 kg/m^2^) compared to first-year students (20.3 ± 2.3 kg/m^2^; *P*=.005). Mean WHR was higher in third/fourth-year students (0.81 ± 0.06 cm) compared to first-year students (0.77 ± 0.04 cm; *P*=.04). Students were primarily sedentary (mean time spent sedentary was 81.7 ± 4.4%) and only engaged in an average of 9.9 ± 8.8 minutes of vigorous activity per day. Our pilot study results indicate that nursing students are highly inactive and that metabolic status based on BMI and WHR is worse in senior students [30].

We observed in our pilot study that nursing students are highly sedentary; however, it is important to note that PA is likely not the only factor that contributes to weight and obesity status in nursing students. For example, nutrition and food intake are directly correlated with BMI and WHR in RNs [31], and increased meal intake and poor nutrition are prevalent in shift workers [32]. As previously mentioned, poor sleep [33,34] and stress all likely contribute to worse metabolic health and overall well-being of nursing students. There is currently no study that examines the association of multiple lifestyle factors (including PA, nutrition, sleep, and stress) and metabolic health in a cohort of nursing students.

### Purpose and Objectives

The current study will expand upon previous research [30] and will characterize the factors that discriminate metabolic health of undergraduate nursing students attending a Canadian university. To this end, the objective of this study is to determine what factors are associated with metabolic health (measured by BMI, WHR, body fat percentage, blood pressure, and fasting glucose) in full-time undergraduate nursing students. More specifically, we will examine whether objectively measured PA, sleep, nutrition, or stress are associated with poor metabolic health status in a cohort of nursing students.

Based on pilot data [30], we believe that senior nursing students will have worse metabolic health (ie, higher BMI, higher WHR, increased body fat percentage, elevated blood pressure, and increased fasting blood glucose) compared to first-year students. We also hypothesize that poor PA participation, poor sleep quantity and quality, increased food intake, poor nutrition, and increased stress will be associated with worse metabolic health in full-time nursing students.

### Significance

The current study will be the first published research to examine the relationship between lifestyle choices and metabolic status in nursing students attending a Canadian institution. More importantly, the results of this study will be used to inform a lifestyle intervention for nursing students. To our knowledge, there are only 2 published PA and lifestyle intervention studies that target nursing students. In one study, nursing students and student midwives (N=182) from the UK were randomized into a control or an intervention group. Students in the intervention group received an education package and created a nutrition and physical activity plan. Following the 4-month intervention, the BMI of the overweight participants decreased, indicating that education and accountability may influence exercise participation in nursing and midwifery students [35]. In a second study, a convenience sample of 30 nursing students from a university in the United States who wanted to increase their PA levels were invited to participate in an exercise intervention. Students were asked to exercise for 30 minutes at least 3 times per week. Following one university semester of the intervention, students had reduced body fat percentages and BMIs, and higher levels of self-reported PA [36]. These studies support the idea that a lifestyle intervention can positively affect metabolic health status in nursing students.

The results of this study will directly inform a lifestyle intervention for nursing students that targets the improvement of their health and well-being, specifically addressing the most prominent factors associated with their poor metabolic health status. For example, if reduced PA, poor nutrition, and lack of sleep are all associated with worse metabolic health in nursing students, the developed intervention will focus on improving these outcomes. The development of an intervention will target the improvement of both the physical and mental health of nursing students. This intervention has the potential to influence future nursing practice since research highlights that RNs who are physically active will be more likely to counsel their patients to be physically active [10].

## Methods

### Overview of Study Design, Timeline, and Participant Selection

In this cross-sectional study, students enrolled in a school of nursing in an Ontario university in Canada will be invited to participate. A member of the research team will approach students in multiple ways, such as through classroom announcements, a post on the online learning system portal, posters, and word of mouth. Members of the research team who will approach and consent students will have no association with the students’ courses or academic work. Each year, the school of nursing enrolls approximately 200 students. We will aim to include approximately half of all students (ie, 80 students from each of the four years of nursing studies) to participate in the study (N=320). Our primary research objective is to examine multiple lifestyle factors (including PA, nutrition, sleep, and stress) and determine whether these factors are associated with metabolic health in full-time undergraduate nursing students; thus, we calculated our sample size based on our pilot data [30], which included an observed coefficient of determination value (R^2^) of 0.25 when we conducted a linear regression that examined whether participation in sedentary, light, moderate, and vigorous activity was associated with BMI. We determined that for a 2-tailed regression analysis with 4 predictors, a total sample size of 87 is required to provide us with statistical power of 0.95. Since we may have more than 4 predictors (participation in sedentary, light, moderate, and vigorous activity; nutrition, which may include total kilocalories (kcals); sleep, which may include total sleep; and stress), we also determined that for a 2-tailed regression analysis with 7 predictors, a total sample size of 103 is required to provide us with statistical power of 0.95. Thus, our sample size of 320 students is more than adequate. We chose to target a total of 320 students as we wanted to have a sufficient representation of those attending the nursing program.

Ideally, we will recruit all participants during 1 academic year. If required, we will extend our recruitment and data collection over a second academic year. Specific inclusion criteria are (1) students enrolled in full-time nursing studies, (2) ≥18 years of age, and (3) signed informed consent. Only nursing students will be included in the current study (ie, there is no non-nursing student control group), since a comparison group is not required to address our research objective of examining discriminators of metabolic status in nursing students. Once the consent form is signed, students will meet with a member of the research team for their study visit (Figure 1). Only 1 study visit is required, which is estimated to take 60-90 minutes in total; therefore, this study involves minimal participant time commitment. Upon study completion, participants will receive a gift card to a popular snack or coffee location on the university campus.

**Figure 1 figure1:**
[figure not shown]
Illustration of the study timeline; BP: blood pressure, DASS: Depression Anxiety Stress Scale, HRV: heart rate variability, IPAQ: International Physical Activity Questionnaire, PA: physical activity, WHR: waist-to-hip ratio.

### Assessments

#### Metabolic Health Measures

Metabolic health will be assessed by measuring obesity (BMI, WHR, body fat percentage), blood pressure, and fasting blood glucose, which are components of metabolic syndrome [37].

Participants will meet with a member of the research team and will complete a demographic questionnaire which includes information related to previous university or college studies, year of study in nursing, general health (ie, presence of any chronic diseases, use of medication), current living arrangements (ie, on-campus or off-campus with a commute), whether students are currently working or volunteering on the side, other health-related habits (such as drinking alcohol and smoking), as well as past history of PA participation. To further understand participation in PA over the past year, participants will complete the Modifiable Activity Questionnaire [38], which has been used to assess associations between physical activity and metabolic health in adults [39]. Participants will have their height (in centimeters) and weight (in kilograms) measured using a stationary research-grade stadiometer and scale. BMI will be calculated from the height and weight measurements: weight (kg)/height (m)^2^ [40]. Waist and hip measurements will be recorded as per the World Health Organization’s (WHO) guidelines using a Gulick tape measure [41]. At each site, 3 measurements will be taken, and they will be repeated if the measurements fall more than 1 centimeter away. The average value will be used to calculate the WHR: waist circumference (cm)/hip circumference (cm). Skinfold measures will be obtained using a Slim Guide skinfold caliper (FitSystems Inc). Measures will be obtained at the triceps, biceps, subscapular, suprailiac, and medial calf. Body fat percentage will be calculated using equations established by Durnin and Womersley (1974) [42].

Resting blood pressure (BP) will be measured using an automated oscillatory device (Omron Healthcare Inc) placed on the nondominant upper arm. Participants will be in a seated position for approximately 5 minutes prior to measurement. Two BP readings will be taken 60 seconds apart. An average of the 2 readings will be used.

Participants will be asked to fast (ie, to consume no food or drink other than water) for 12 hours prior to their study visit. Blood glucose will be measured using a standard glucometer; the third finger of the nondominant hand will be cleaned with an alcohol wipe and lanced using a single-use lancet. Blood will be collected on a test strip and measured via the glucometer.

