### Statistical Analysis

The demographic characteristics of the participants will be assessed using descriptive statistics. The association between metabolic status (BMI, WHR, body fat percentage, blood pressure, and fasting blood glucose) and PA outcomes, sleep quantity and quality, nutrition, and stress will be examined by linear regression analyses. To examine differences by year of study, 1-way analyses of variance (ANOVAs) will be conducted comparing metabolic health status, PA, sleep, nutrition, and stress. Bonferroni post-hoc testing will be conducted if significant group differences are present. To determine the association between PA, sleep, nutrition, and stress with metabolic health (ie, BMI, WHR, blood pressure, blood glucose), we will conduct linear regression analyses in all nursing students, and by year of study.

To determine the ability of PA, sleep, nutrition, and stress to discriminate prevalent overweight and obesity, participants will be placed into one of 2 groups: overweight or obese versus not overweight or obese, based on the WHO’s BMI and WHR cut-offs [40]. Logistic regression and receiver operating characteristic (ROC) curves will be constructed for each lifestyle variable [expressed as area under the ROC curves (AUROC) with 95% confidence intervals (CI)]. Similar analyses will be conducted using a composite indicator of metabolic status (incorporating obesity status, blood pressure, and fasting blood glucose). Additional analyses adjusted for age, gender, year of nursing study (including exposure to practicum), semester of school, and other potential confounding variables (such as prior physical activity habits) will be conducted as deemed necessary. Statistical analyses will be performed in Stata (version 16.1, StataCorp LLC).

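### Fasting glucose is described as a single glucometer reading while girths and blood pressure are averaged; a second strip would recover power in the by-year regressions

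*Protocol article*

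**What the plan says.** Under Metabolic Health Measures, the protocol article describes one lancing of one finger and one reading: "Blood glucose will be measured using a standard glucometer", and then "Blood will be collected on a test strip and measured via the glucometer". It mentions no repeat and gives no meter model or accuracy.

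The same section fixes replication for two other measures:
- Waist and hip: "At each site, 3 measurements will be taken, and they will be repeated if the measurements fall more than 1 centimeter away". The average goes into the waist-to-hip ratio.
- Blood pressure: "Two BP readings will be taken 60 seconds apart", and "An average of the 2 readings will be used".

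The Statistical Analysis section uses glucose in two ways. It is a continuous outcome in linear regression ("The association between metabolic status (BMI, WHR, body fat percentage, blood pressure, and fasting blood glucose) and PA outcomes"), and a second sentence, which also lists blood glucose, plans these regressions in all students and separately by year of study. Glucose also enters a composite described as incorporating obesity status, blood pressure and fasting glucose, for which analyses similar to the logistic and ROC analyses are planned. No glucose cut-off is stated.

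The design section targets 80 students from each of four years, 320 in total.

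**The concern.** A point-of-care meter has random error from strip to strip. If true fasting glucose varies little among undergraduates, that error can be an appreciable part of the observed variance. The plan averages repeat readings for girths and blood pressure, but as described takes glucose at face value from one strip.

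What is at stake is precision. Random error in the outcome adds to the residual variance, so R² falls and an association is harder to detect. A sample of 320 can absorb a good deal of this; a single-year regression of about 80 has much less to spare. The error also passes into the composite, but the article does not say how glucose enters it, so that effect cannot be sized.

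**Working it through.** **The plan's own figure.** There is none to reproduce: the article gives no glucose mean, SD, meter error or cut-off.

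**Inputs from the protocol article.** N=320 in total and about 80 per year; up to 7 predictors; R² of 0.25, observed in the pilot for BMI on activity and borrowed here for glucose.

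**Assumed inputs.** Between-student SD s = 0.35 or 0.45 mmol/L; random meter SD e = 0.2, 0.3 or 0.4 mmol/L; alpha 0.05 (the article states none); errors of the two strips independent.

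**Formulas.**
- Reliability of one reading: s²/(s² + e²). Of the mean of two: s²/(s² + e²/2).
- Observed R² = 0.25 × reliability.
- f² = R²/(1 − R²), with noncentrality λ = f² × n.
- Power = probability that a noncentral F with 7 and n − 8 degrees of freedom exceeds its 5% critical value (2.14 at n=80).

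**No meter error, n=80.** f² = 0.25/0.75 = 0.333; λ = 26.7; power 0.97.

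**Worst pair (s=0.35, e=0.4), n=80.**
- One reading: reliability = 0.1225/(0.1225 + 0.16) = 0.43; R² = 0.108; f² = 0.122; λ = 9.7; power 0.55.
- Mean of two: reliability = 0.1225/(0.1225 + 0.08) = 0.60; R² = 0.151; f² = 0.178; λ = 14.3; power 0.75.

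**All six pairs, n=80, true R² 0.25.**

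| s | e | Reliability, one | Reliability, two | Power, one | Power, two |
|---|---|---|---|---|---|
| 0.35 | 0.2 | 0.75 | 0.86 | 0.87 | 0.93 |
| 0.35 | 0.3 | 0.58 | 0.73 | 0.72 | 0.86 |
| 0.35 | 0.4 | 0.43 | 0.60 | 0.55 | 0.75 |
| 0.45 | 0.2 | 0.84 | 0.91 | 0.92 | 0.95 |
| 0.45 | 0.3 | 0.69 | 0.82 | 0.83 | 0.91 |
| 0.45 | 0.4 | 0.56 | 0.72 | 0.70 | 0.85 |

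**Whole sample, N=320.** In the worst pair with one reading, λ = 0.1216 × 320 = 38.9 and power is 0.999. The other pairs are higher still.

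**If glucose is less predictable than BMI.** With an assumed true R² of 0.05, power at N=320 is 0.86 without error, 0.44-0.78 with one reading and 0.60-0.82 with two. At n=80 it is only 0.24 even without error, and a second strip would not rescue the by-year analysis.

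**Link to the sample size section.** The article asks for 103 students for power 0.95 with 7 predictors. At alpha 0.05 the calculation above needs only 73, which is why 80 gives 0.97 here. Since alpha is not stated, the article's figure cannot be called wrong; a stricter alpha would lower every power above.

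**The case against.** The strongest reply is that nothing about glucose in this calculation comes from the documents. Spread and meter error are assumed, and the R² is for another outcome. The whole-sample regressions lose nothing that matters at R² 0.25. Skinfolds, height and weight are also described without replicates, so unequal replication is not in itself an inconsistency. A journal article may also condense a procedure that already duplicates the strip. These points stand. They confine the concern to precision in the smaller regressions, but they do not remove it: the article gives replicate counts for girths and blood pressure, and for glucose it describes one strip.

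A reader might infer more than the documents support:
- *Meter error swamps the true range.* It exceeds the true spread in only one of the six assumed pairs. On a wider grid (true SD 0.3-0.6, meter SD 0.1-0.5) it at least equals the spread in 6 of 20.
- *Most raised values would be false.* The article states no glucose cut-off and no raised-glucose class. With an illustrative cut-off of 5.6 mmol/L and assumed means of 4.6-5.2, the false share on that wider grid runs from 9% to 99% and passes half in 42 of 80 scenarios. That range establishes nothing about this plan.
- *Glucose associations are biased toward null.* Glucose is the outcome in these regressions, and random error in an outcome leaves the slopes unbiased.
- *Non-fasted readings would be analysed as fasting.* The 12-hour fast is defined. How it is checked is detail that an article may leave to the full protocol.

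**Conclusion.** The concern holds as a minor point of measurement precision. As described, glucose is read once, while girths and blood pressure in the same section are averaged. With a true R² of 0.25, power at N=320 is essentially unaffected. In the by-year regressions it falls from 0.97 to 0.55-0.92 with one reading, and the mean of two brings it back to 0.75-0.95.

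These figures depend on the assumed SDs, alpha 0.05, 7 predictors, the BMI-based R² and independent strip errors. Any error shared by both strips would shrink the gain. No bias in the glucose slopes and no excess of false raised values has been shown.

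**What to change.** In the glucose paragraph of Metabolic Health Measures, state that two strips will be read from the same lancing on the same meter and that their average will be used, as is already done for blood pressure. If the full procedure already does this, saying so is enough.

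The cost is one more strip per student, about 320 in all, with no further lancing. Duplicates reduce only strip-to-strip error; meter calibration error and day-to-day variation within a student remain. The change has to be made before data collection, because a second reading cannot be recovered afterwards.
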